## Methods

### Study Design, Setting, and Recruitment

This is a repeated-measure, double-blinded, placebo-controlled, randomized trial, administered at a single site, the University of Florida (UF). This clinical trial was registered in the United States National Library of Medicine through ClinicalTrials.gov (NCT05377424).

Patients living with ALS will be recruited from the UF ALS clinic, as well as through flyers, word of mouth, and the study registry website. Patients who meet the study criteria will be identified by the study physicians through the UF adult neuromuscular clinic. Healthy age-matched controls will be recruited via advertising for the study on ClinicalTrials.gov, StudyConnect, social media for the UF Clinical and Translational Science Institute, and flyers throughout the local community. Additional potential healthy controls will be identified from the Pepper Center Registry maintained by the UF Institute on Aging, and institutional review board (IRB)–approved flyers will be sent to their address. Study interventions will occur at a university-based clinical research center located in Gainesville, FL.

### Inclusion Criteria

Eligible participants include nonsmoking adults diagnosed with ALS or age-matched unaffected controls, aged 21-80 years. Eligible participants will have El Escorial diagnostic classification of probable or definite ALS and vital capacity (VC) ≥60% of predicted value; we seek to treat participants before they approach respiratory failure and need for mechanical ventilation, which typically occurs when VC falls below 50% predicted [48]. The ALS Functional Rating Scale-Revised (ALSFRS-R) consists of 12 ordinal items of 5 points (rated 0-4) each, which describe impairments in different systems functionally, where a score of “4” reflects normal function and “0” reflects profound dysfunction [49]. Scores below 2 for respiratory and bulbar items typically reflect severe functional impairment (ie, need for supplemental tube feeding and continuous use of respiratory support). Clinically prescribed ALS medications must be at a stable dose for 30 days.

### Exclusion Criteria

Participants (both affected and controls) are ineligible if they are pregnant, have an active respiratory infection, took antibiotics within 4 weeks of recruitment, are diagnosed with another neurodegenerative disease, have symptomatic cardiovascular disease or dysrhythmias, have a BMI of >35 kg/m^2^, have a seizure disorder, use respiratory inhalers daily for airway disease, or require external respiratory support while awake and upright. In addition, the following conditions are exclusionary for the use of istradefylline: routine use of CYP3A4 inducers (eg, carbamazepine, rifampin, phenytoin, and St John’s Wort), history of moderate renal impairment or severe hepatic impairment, and history of hallucinations or psychosis.

### Rationale for Including Age-Matched Controls

AIH has shown to improve cognitive and exercise performance by improving hemodynamics and work capacity in healthy older adults [50,51]. While effects of AIH and istradefylline have been tested separately in healthy older adults, there is a lack of evidence regarding the additive effects of pairing istradefylline with AIH. Since older adults are the individuals who typically have the greatest need for rehabilitation, we are interested to test whether combined istradefylline and AIH can augment respiratory motor plasticity in healthy older adults.

Healthy older adults have been previously included in clinical trials to evaluate the exposure-response relationship and pharmacokinetic disposition of istradefylline in patients with PD [45,52]. By including healthy older adults in our study, we can determine whether any observed differences with paired AIH and istradefylline among individuals with ALS are specific to ALS or are potentially more generalizable to the older adult population.

### Study Procedures

The SPIRIT (Standard Protocol Items: Recommendations for Interventional Trials) flow chart with all study procedures can be found in Table 1.

**Table 1 table1:** SPIRIT (Standard Protocol Items: Recommendations for Interventional Trials) flow chart with a schedule of enrollment, interventions, and assessments.

Activity			Study period												
			Enrollment		Allocation		Postallocation visits separated by 2 weeks (±5 days), 6-10 weeks total								2-week follow-up
			T–1		T0		T1	T2		T3		T4		T5	
**Enrollment**															
	Eligibility screen	✓													
	Informed consent	✓													
	Allocation			✓											
**Interventions**															
	Istradefylline + AIH^a^					—^b^		—	—		—				
	Istradefylline + sham AIH					—		—	—		—				
	Placebo + AIH					—		—	—		—				
	Placebo + sham AIH					—		—	—		—				
**Assessments**															
	Study completion rate												✓		
	Adverse events					✓		✓	✓		✓		✓		
	Vital signs (HR^c^/BP^d^)					✓		✓	✓		✓				
	Participant-reported symptoms					✓		✓	✓		✓				
	Borg dyspnea scale					✓		✓	✓		✓				
	Laboratory tests					✓		✓	✓		✓				
	Minute ventilation					✓		✓	✓		✓				
	MIF^e^					✓		✓	✓		✓				
	PCF^f^					✓		✓	✓		✓				
	MIP^g^					✓		✓	✓		✓				
	SNIP^h^					✓		✓	✓		✓				
	Pinch force					✓		✓	✓		✓				

^a^AIH: acute intermittent hypoxia.

^b^Administered at 1 visit, in randomized order.

^c^HR: heart rate.

^d^BP: blood pressure.

^e^MIP: maximal inspiratory pressure.

^f^PCF: peak cough flow.

^g^MIP: maximal inspiratory pressure.

^h^SNIP: sniff nasal inspiratory pressure.

### Ethical Considerations

Ethical approval was granted by the UF IRB (IRB 202101568) on May 16, 2022. The US Food and Drug Administration provided clearance for off-label investigational use of istradefylline as described in the protocol (investigational new drug application, approved April 8, 2022; 156267). Informed consent will be obtained in writing from all participants prior to enrollment by study team members. See Multimedia Appendices 1 and 2 for informed consent forms. Participants were informed they would be able to withdraw from the study at any time for any reason. This work is supported by the ALS Association. Outside of the human research protection review, the funding sponsor does not have a direct role in directing the study design; collection, management, analysis, and interpretation of data; writing of the report; or the decision to submit the report for publication.

Health information will be collected, used, and shared with others (ie, clinical and research staff and the UF Research Participant Payment team) to determine if interested individuals are eligible to participate, and then as part of the participation in the study. The following information may be collected, used, and shared with others: medical history, including past conditions and surgeries, medications, and information related to diagnosis of ALS; social security number (for reimbursement purposes); demographic information; contact information; and the results of the research tests done for this study. The research team may collect this information from other health care providers, such as laboratories, which are a part of this research, as well as health care providers that are not part of this research (other doctors, hospitals, or clinics). Other professionals at the UF or UF Health Hospital who provide study-related care, and the UF IRB, may also collect health information. Participants will be informed of the collection and protection of health information collected as part of the informed consent process. Health information and study data will be stored in locked filing cabinets or on computer servers with secure passwords or encrypted electronic storage devices, as required by UF policy.

Participants will be compensated US $20 for the screening visit and US $120 for each treatment visit, via prepaid Visa gift cards. Additionally, overnight hotel expenses will be covered by the study for participants traveling from out of town, and lunch will be provided during treatment visits.

### Screening

Interested individuals who meet the basic study criteria, agree to participate, and sign the IRB-approved informed consent form will undergo further screening procedures prior to the first interventional visit. Prospective participants will be informed of the eligibility criteria, study procedures, participation risks, privacy and safety precautions in place, alternatives to study participation, and the right to withdraw from the study at any time. The study coordinator will schedule visits and communicate with participants by phone and email. The study coordinator or a designated investigator will complete consenting and screening tests (Figure 2).

**Figure 2 figure2:**
[figure not shown]
Screening procedures. AHI: apnea-hypopnea index; ALSFRS-R: Amyotrophic Lateral Sclerosis Functional Rating Scale-Revised; ECG: electrocardiogram; HR: heart rate; VC: vital capacity.

Screening tests shall include:

Patient demographic information and medical history: sociodemographic (age and sex), anthropometric (height and weight to calculate the BMI), and general clinical data (medical history, comorbidities, and medications).VC: the maximal volume of gas that can be exhaled, following full inspiration. Upright VC will be administered per American Thoracic Society and European Respiratory Society guidelines [53,54]. Individuals with less than 60% of predicted VC will be ineligible for further participation in this study.12-lead electrocardiogram: cardiac rate and rhythm will be evaluated. The presence of resting tachycardia (HR >110 bpm), atrial fibrillation, or other dysrhythmias will exclude people from participation.STOP-BANG (Snoring, Tiredness, Observed Apnea, High BP-BMI, Age, Neck Circumference, and Gender) questionnaire: questionnaire to estimate the risk of obstructive sleep apnea (OSA) [55]. A meta-analysis found a STOP-BANG score of ≥3 had excellent sensitivity and high discriminatory power to exclude moderate to severe OSA [56].Overnight sleep monitor: participants will wear an overnight sensor that noninvasively monitors arterial oximetry and breathing parameters (Nox T3s; Nox Medical) to estimate the severity of sleep-disordered breathing [57]. If clinically significant OSA (apnea-hypopnea index [AHI] >10 events/hour) is detected, participants will be offered a referral to a clinical sleep specialist for further evaluation. If they choose to pursue clinical treatment for sleep apnea, they will be withdrawn and eligible to rescreen for participation after receiving 3 months of treatment. If they choose not to seek treatment, they will be included in the study. Participants with severe OSA AHI >30 events/hour will be ineligible.

### Study Visits

After providing written consent and completing screening, participants will complete 4 individual study visits separated by 2 weeks (±5 days). Visits will include (1) istradefylline + AIH, (2) placebo + AIH, (3) istradefylline + sham AIH, and (4) placebo + sham AIH (Figure 3), in randomized order. Participants will undergo single sessions of each treatment condition. They will be instructed to avoid exercise, caffeine, and nicotine products prior to testing for a minimum of 6 hours and to avoid eating within 1 hour of sessions.

**Figure 3 figure3:**
[figure not shown]
Study design. The gray bars with arrows represent the timing of data collection procedures. AIH: acute intermittent hypoxia; IST: istradefylline.

Session order was determined by a random number table generated in advance of the enrollment of the first participant and maintained by the investigational pharmacist. Participants and investigators will remain blinded to istradefylline versus placebo for study administration and data analysis. Participants as well as the investigator collecting test outcomes will be blinded to AIH versus sham AIH. Prior to each study visit, the investigational pharmacist will inform the study coordinator which gas to administer during intervention (ie, hypoxic air for AIH vs normoxic air for sham AIH). Study team members conducting gas treatment cannot be fully blinded to AIH versus sham AIH due to monitoring of pulse oximetry oxygen saturation (SpO_2_), which is necessary for safety; thus, the investigator collecting testing outcomes will not be present during gas administration.

Participants will sit upright in a chair with the head and trunk supported while breathing through a sealed face mask. Resting ventilation, respiratory muscle activation, maximal respiratory pressures, maximal pinch force, and blood draws will be completed at the start of each study visit, then participants will receive study medication to be taken orally. After a 4-hour break, all outcome-measure testing will be repeated, followed by gas delivery. Postintervention testing will occur at 60 and 120 minutes following gas delivery. Table 2 delineates outcome measures taken at each time point.

Study visits are expected to last 7-8 hours, including equipment setup, repeated outcome measurements, oral administration of study medication, waiting periods, gas delivery, patient positioning and pressure relief, rest, and snacks or meal breaks.

**Table 2 table2:** Timing of variable measurements throughout study visit.

	Baseline	4 h post drug	Gas delivery	60 min post gas	120 min post gas
Adverse events	✓	✓	✓	✓	✓
Vital signs (HR^a^/BP^b^)	✓	✓	✓	✓	✓
Participant-reported symptoms	✓	✓		✓	✓
Borg dyspnea scale			✓		
Laboratory tests	✓	✓		✓	
Minute ventilation	✓	✓	✓	✓	✓
MIF^c^	✓	✓		✓	
PCF^d^	✓	✓			✓
MIP^e^	✓	✓		✓	
SNIP^f^	✓	✓			✓
Pinch force	✓	✓			✓

^a^HR: heart rate.

^b^BP: blood pressure.

^c^MIP: maximal inspiratory pressure.

^d^PCF: peak cough flow.

^e^MIP: maximal inspiratory pressure.

^f^SNIP: sniff nasal inspiratory pressure.

### Independent Variable—A2A Antagonist Versus Placebo

During each study visit, participants will take a single, 20 mg NOURIANZ pill or an identical-appearing placebo. The study agent will be taken after the completion of baseline breathing tests. Study gas delivery will begin 4 hours later. During the 4-hour waiting period, participants will have a private room with a bed and recliner and access to water, snacks, and a light meal, as well as bathroom facilities. Participants will also be free to move about the research unit.

### Independent Variable—AIH Versus Sham AIH

Following the 4-hour break and second round of testing, participants will undergo a 45-minute session of either AIH (up to 1 minute of 9%-10% O_2_ with 2 minutes of 21% O_2_ for 15 cycles; target SpO_2_ nadir 82%-85%) or sham AIH (Figure 4). During sham AIH administration, the 1-minute periods of study gas will use a gas bag containing 21% O_2_, with 2-minute room-air periods, so that participants are breathing normoxic air for the entire session. Outcome measures will be repeated 60 and 120 minutes after gas delivery.

A schematic of the respiratory circuit is shown in Figure 5. Participants will sit upright in a chair with the head and trunk supported while breathing through a sealed face mask (Hans Rudolph 7450). The face mask will be connected to a 2-way nonrebreathing valve (Hans Rudolph 2700) that allows the exhaled breath to escape to room air. A pressure transducer (MK1S, GM Instruments) and gas analyzer (Gemini CO_2_ & O_2_ monitor; CWE Inc) will be connected directly to the face mask connector. A pneumotachograph (Hans Rudolph 4813) will be connected to the inspiratory port of the nonrebreathing valve. Gas bags will be connected to a 3-way stopcock valve (Hans Rudolph 2100), and the direction of the valve will be manually alternated between the study gas (1-minute intervals) and normoxic room air (2-minute intervals). Respiratory data will be recorded during gas delivery, using a data acquisition system (PowerLab 16/35 and PowerLab C; ADInstruments).

Respiratory rate, targeted O_2_ value, end-tidal CO_2_, HR/rhythm, and SpO_2_ will be continuously monitored during the testing sessions. Multichannel sEMG (Trigno Centro; Delsys) will also be recorded from respiratory muscles (bilateral submental, scalene, sternocleidomastoid, second parasternal, and diaphragm) as well as abductor pollicis muscle during testing and captured in real time in LabChart (AD Instruments). At the end of each 1-minute hypoxic (or sham-hypoxic) presentation, participants will report their rating of dyspnea (10-point modified Borg scale). For every fifth presentation, noninvasive BP will be taken. We will establish an individualized communication plan (eg, hand signal, head tilt, call switch, etc) prior to study gas administration to ensure that all participants can alert the investigator of any discomfort, shortness of breath, or requests to remove the face mask.

**Figure 4 figure4:**
[figure not shown]
Schematic of acute intermittent hypoxia (AIH) and sham AIH interventions. AIH sessions will consist of 1-minute intervals of hypoxia (10% O2) separated by up to 2-minute intervals of normoxic room air (21% O2). Sham AIH will use identical equipment, but the gas bag will contain 21% O2.

**Figure 5 figure5:**
[figure not shown]
Schematic of the respiratory circuit for gas delivery. AIH: acute intermittent hypoxia; BP: blood pressure; ETCO2: end-tidal CO2; ETO2: end-tidal O2; HR: heart rate; PL: PowerLab; SpO2: pulse oximetry oxygen saturation.

### Safety Considerations

The target SpO_2_ during AIH is 82%-85% O_2_. If the SpO_2_ reaches the lower limit of the target range, gas delivery will be switched to the normoxic recovery time. Subsequent hypoxia durations will also be reduced by 5 seconds. AIH will be stopped in the unlikely event the HR increases or decreases >30% from the resting value, or systolic BP changes >30% from the resting value. The expected acute physiological response to hypoxia is a stable or decreased CO_2_ due to increased ventilation. However, if end-tidal CO_2_ increases >3 mmHg above baseline, we will shorten AIH bouts using the same process described above for SpO_2._ Additional stopping criteria include a respiratory rate of >30 that fails to normalize within 1 minute of normoxia, SpO_2_ <82% that fails to normalize within 1 minute of normoxia, or SpO_2_ <82% occurring within 30 seconds of hypoxia initiation.

In the unlikely event that a participant is injured as a direct result of participation in this study, professional services rendered by any UF Health Science Center health care provider will be provided without charge. These health care providers include physicians, physician assistants, nurse practitioners, dentists, and psychologists. Any other expenses, including UF Health hospital expenses, will be billed to the participant or his or her insurance provider.

Safety oversight will occur internally through the local IRB and a data safety monitoring board (DSMB). The DSMB was convened before enrollment of the first patient, after completion of the first 3 participants, and at least annually thereafter. The DSMB includes 3 members—1 expert in intermittent hypoxia, 1 clinical medicine expert who interprets or prescribes respiratory testing and treatment, and 1 rehabilitation specialist.

Testing and enrollment of participants will be paused, and DSMB will convene for any of the following events: (1) any clinically significant respiratory event, (2) a clinically significant cardiovascular event, or (3) a serious adverse event as defined by the UF IRB. Should any of the events occur, research staff shall inform the IRB and the DSMB. Any subsequent study activities would only be resumed when cleared or the protocol modified by the IRB and DSMB. As of January 2025, these serious events have not occurred, and the DSMB has only been convened for planned early and annual meetings.

### Aim 1 Dependent Variables

Adverse events: adverse events will be tracked and recorded per usual IRB requirements and reported as the Aim 1 primary safety outcome. It is hypothesized that there will be no difference in the rates of adverse events among study conditions.Cardiopulmonary responses: vital signs and cardiac rhythm will be monitored throughout administration of each test condition. These measurements will be used in real time to monitor intervention safety, particularly during gas administration, as outlined under “safety considerations.” Additionally, 1-minute averages of HR, BP, end-tidal CO2, and SpO2 will be compared at baseline, 60 minutes, and 120 minutes following study gas delivery. It is anticipated that these measurements will remain stable at these time points.Laboratory tests: baseline blood samples will be drawn for each session and include routine clinical laboratory tests (complete blood count, chemistry) and uric acid. Blood samples will be drawn for plasma istradefylline levels at the baseline of each study visit and 4 and 6 hours after ingestion of the study medication. It is anticipated that laboratory test values will remain stable across visits. Participants will be offered an intravenous line to be placed at the start of the visit to avoid multiple venipunctures.Participant-reported symptoms: participants will complete 10-point visual analog scales to rate the intensity of symptoms (of dyspnea, dizziness, weakness, fatigue, nausea, and involuntary movements) at the following time points: baseline, 4 hours after taking the drug or placebo, and 60 and 120 minutes after gas delivery. It is anticipated that symptoms will remain stable across time points and visits.Study completion rate: the primary feasibility outcome will be the proportion of participants who complete all study visits. Additional feasibility metrics will include screening failures, proportions of interested participants who are ineligible, and timeliness of study milestones.

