**Figure 1 figure1:**
[figure not shown]
Competing serotonin- (Q) and adenosine-driven (S) pathways to phrenic motor facilitation. Listed on the right are factors that impact serotonin-dominant plasticity due to increased adenosinergic “S” pathway inhibition. By combining istradefylline with mild acute intermittent hypoxia (AIH), this protocol aims to minimize crosstalk inhibition by reducing S to Q pathway inhibition, allowing full expression of the “Q” pathway.

Elevated spinal adenosine is a characteristic of neurodegenerative diseases, such as ALS [41,42]. In the SOD1^G93A^ (copper zinc superoxide dismutase 1) mouse model of ALS, A_2_A receptor signaling contributed to motor neuron degeneration, while A_2_A receptor antagonism delayed disease progression [42]. A_2_A antagonism can also have neuroprotective and anti-inflammatory effects in motor neurons [43]. NOURIANZ (istradefylline) is a highly selective A_2_A receptor antagonist currently approved for use in adults with PD to offset inhibitory effects of upregulated A_2_A receptors on D2 dopamine receptors of the basal ganglia [44]. Istradefylline reduces daily “off” time in people with PD, improving periods of mobility, and is reported safe and well tolerated [45]. Dyskinesia (5%) and hallucinations (3.4%) were the most common side effects associated with longer-term use [46], but cognition, sedation, or risk of cardiovascular events were not impacted [47]. Considering the demonstrated safety of chronic istradefylline in PD and healthy controls, we hypothesize that this brief, temporary treatment will be safe in ALS.

We further hypothesize that the combination of istradefylline and AIH, in patients with ALS, will elicit greater gains in respiratory and nonrespiratory motor function than either intervention alone, and that will contribute to improvements in breathing and motor function. In a rodent model of phrenic motor neuron death, significant A_2_A receptor upregulation preceded motor neuron loss, but the coadministration of istradefylline improved motor neuron survival and maintained diaphragm function [43]. The information gained in this investigation will help us optimize intervention approaches for future studies of repeated, daily AIH as a rehabilitation tool. Thus, this study represents an important step in the iterative process of moving AIH protocols toward clinical practice.

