### Aims

The objective of this study is to evaluate single and combined effects of selective A_2_A receptor antagonism and AIH on respiratory strength, resting breathing, and participant-reported symptoms in adults living with ALS and age-matched unaffected adults. The following two aims are proposed to test the hypotheses:

Aim 1: a single 20 mg istradefylline dose prior to AIH is safe and feasible. Dependent variables will include rate of adverse events (primary outcome), acute changes in vital signs (HR, respiratory rate, blood pressure [BP], etc), patient-reported symptoms (dyskinesias and dizziness), and study completion.

Aim 2: a single 20 mg istradefylline dose prior to AIH improves respiratory motor function when compared to either intervention alone. Dependent variables will include resting tidal volume (primary outcome), breathing rate and minute ventilation, respiratory muscle assessments via multichannel surface electromyography (sEMG), cough force, maximal inspiratory pressure (MIP), and maximal finger pinch force.

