## Discussion

This clinical trial will evaluate the effects of istradefylline paired with AIH on breathing function in people with ALS and unaffected age-matched controls. It is anticipated that this combined treatment will be safe and feasible, and that when combined, istradefylline and AIH will result in greater gains in respiratory function (eg, increased tidal volume and increased MIP) than either treatment alone.

Individuals living with ALS face progressive neuromuscular disease that leads to paralysis from motor neuron death. While recently approved ALS drugs offer more options to treat the disease, combinatorial strategies will likely be needed to preserve motor function and independent breathing for as long as possible. To our knowledge, this is the first clinical trial to assess the combined effects of A_2_A receptor antagonism and AIH in ALS.

AIH is easy to apply and well-tolerated by most individuals, including people with ALS in a preliminary study conducted by our group [22]. In several studies of humans with chronic spinal cord injury, similar AIH protocols did not lead to adverse events [18,65-70]. We expect AIH will, likewise, be safe and well-tolerated by people with ALS and age-matched controls in this study.

NOURIANZ (istradefylline) has been studied extensively both in participants living with PD and in healthy adult participants. Population pharmacokinetic studies were summarized previously and included both single and repeated daily administration (up to 16 weeks) of istradefylline doses ranging between 10 and 200 mg [52]. Safety was established in participants living with PD and unaffected older participants, with few and minor side effects. In controlled trials, the most common adverse events with repeated daily treatment of istradefylline included dyskinesias, dizziness, hallucinations, and insomnia. These adverse events occurred more frequently after treatment with 40 mg of istradefylline [52]. As this study will use a treatment dose of 20 mg of istradefylline, we anticipate this therapy will be safe and well tolerated by participants with ALS as well as age-matched controls.

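### The symptom scale leaves out hallucinations and insomnia, two of the four istradefylline adverse events the article names, and stops about 7 hours after the dose, so both rest on general adverse-event recording

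*Protocol article*

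**What the plan says.** Three parts of the protocol article bear on this point.

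- **The drug's known events.** The Introduction (text after Figure 1) states: "Dyskinesia (5%) and hallucinations (3.4%) were the most common side effects associated with longer-term use". The Discussion gives a list of four: "the most common adverse events with repeated daily treatment of istradefylline included dyskinesias, dizziness, hallucinations, and insomnia". Exclusion Criteria bars people with a "history of hallucinations or psychosis" from the trial on account of the drug.
- **The symptom scale.** The Aims section names the Aim 1 symptoms as "patient-reported symptoms (dyskinesias and dizziness), and study completion". Aim 1 Dependent Variables sets out the instrument: participants use 10-point visual analog scales to "rate the intensity of symptoms (of dyspnea, dizziness, weakness, fatigue, nausea, and involuntary movements) at the following time points", namely "baseline, 4 hours after taking the drug or placebo, and 60 and 120 minutes after gas delivery". The article expects these ratings to stay stable.
- **Adverse events.** The same section says "adverse events will be tracked and recorded per usual IRB requirements and reported as the Aim 1 primary safety outcome" and hypothesizes equal rates across conditions. Table 2 ticks adverse events at all five points within a visit. Table 1 ticks them at all four visits and at the 2-week follow-up (T5).

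**The concern.** The article fixes the scale item by item and time by time. Measured against the article's own list of drug events, the scale asks about two of four. Hallucinations are missing, although the article gives a rate for them and excludes people with a history of them. Insomnia is missing too, and the timing alone would rule it out, because every rating is made on the day of dosing before the participant has slept.

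A symptom that is rated at fixed times gives a count for each condition with the same effort in every session. An event that has to be recalled at the next contact, up to 19 days later, is more easily forgotten or left without a firm date. If only a share *s* of such events is reported in every condition, the observed difference between conditions is *s* times the true difference. Under-reporting thus moves the comparison toward the result the article hypothesizes. In a trial this small, one unreported case can be the difference between one event and none.

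**Working it through.** **1. Coverage of the named events**

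| Event named in the Discussion | Item on the scale? |
|---|---|
| Dyskinesias | Yes, as involuntary movements |
| Dizziness | Yes |
| Hallucinations | No |
| Insomnia | No |

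Two of four are covered. The other four items (dyspnea, weakness, fatigue, nausea) are not on that list.

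**2. Time from dose to last rating**

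Inputs: gas begins 4 h after the drug (section on the A2A antagonist versus placebo), the gas session lasts 45 min (section on AIH versus sham AIH), and the last rating is 120 min after gas (Table 2).

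- 240 + 45 + 120 = 405 min = 6.75 h.
- If the second round of testing comes after the 4 h wait and takes 15 to 45 min (assumed; the article gives no duration), the result is 7.0 to 7.5 h.

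Check against the article's own figures: visits are expected to last 7 to 8 h, which fits 6.75 h plus setup and baseline testing. The 60-minute post-gas point falls at 240 + 45 + 60 = 345 min = 5.75 h, which fits the stated 6-hour blood sample.

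**3. Gap to the next scheduled adverse-event assessment**

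Visits are 2 weeks (±5 days) apart: 14 − 5 = 9 days to 14 + 5 = 19 days. After the fourth session, the next assessment is the 2-week follow-up.

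**4. How much one case could matter**

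The article gives no rate for a single dose and none for insomnia. Suppose, as an assumption, that the long-term hallucination rate of 3.4% applied per participant. The chance of at least one case is 1 − (1 − 0.034)^n. If no case is seen, the one-sided 95% upper limit for the true rate is 1 − 0.05^(1/n).

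| n | Source of n | P(at least one case) | Upper limit if none seen |
|---|---|---|---|
| 16 | sample-size calculation | 42.5% | 17.1% |
| 24 | target allowing for attrition | 56.4% | 11.7% |
| 32 | 16 in each of two groups (Abstract) | 66.9% | 8.9% |

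The middle column is better read as an upper-end illustration. The 3.4% is tied to longer-term use, whereas each participant here takes two single active doses of 20 mg. The Discussion reports these events as more frequent at 40 mg, and people with a history of hallucinations are excluded. The last column shows that even complete ascertainment would leave the absence of cases only weakly informative.

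**The case against.** A reader might infer that hallucinations and insomnia are never asked about and that the safety conclusion misses them. The article does not support either statement.

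- The primary safety outcome is adverse events, not the scale. Either event would count there if reported, and recording continues past the day of dosing through the later visits to the 2-week follow-up.
- The article does not say whether adverse events are elicited by checklist, open question or spontaneous report. An article commonly leaves that to the full protocol, so its silence does not show that nothing is asked.
- A reader might also fear that events after one session are charged to the next condition. Baseline recording comes before that day's study drug, so an event reported there cannot be due to that day's condition. With an onset date it belongs to the interval after the preceding session, and attribution is largely recoverable.
- The list of four events comes from repeated daily treatment, and Aim 1 names only dyskinesias and dizziness as symptoms of interest. The scale covers both, so there is no internal contradiction.

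All of this stands, and it limits the point to one of ascertainment. It does not remove it. The scale is specified in the article and omits two events that the article itself calls common with the drug. The general recording that must pick them up is next scheduled 9 to 19 days later.

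**Conclusion.** The point holds as a minor limitation of ascertainment. The structured scale covers two of the four named drug events and ends about 7 hours after the dose (6.75 h from the stated intervals). Hallucinations and insomnia therefore rest on general adverse-event recording, which may under-count them and, to that extent, favours the hypothesis of no difference among conditions.

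The size of the effect cannot be derived from the article, because it gives no rate after single 20 mg doses and no share of events that general recording would catch. The true rate may be well below 3.4%. The safety conclusion is not voided, but stable scores on the scale say nothing about the two events it does not ask about.

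**What to change.** - Add an item on hallucinations or unusual perceptions to the existing visual analog scales, at the same four times.
- At the adverse-event assessments already scheduled (the next visit's pre-dose baseline, and T5 after the last session), ask specifically about sleep and unusual perceptions on the night after the preceding session. Count any event under that session's condition.
- Optionally, make a next-day check by phone or email, which the study coordinator already uses to communicate with participants.
- In the report, do not present stable symptom scores as covering events the scale did not ask about.

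The cost is slightly longer forms and an amendment to the IRB-approved forms, plus a little staff time if the next-day check is used. By January 2025, 10 participants with ALS and 5 controls had completed all procedures, and the last participant is due to finish by December 2025, so new items may reach only part of the sample. If so, report for how many sessions the questions were asked. The reporting restriction applies in any case and costs nothing.
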